### Statistical analysis

2.9

The software SPSS25.0 was used for statistical analysis of data. The statistician will be blinded to the whole trial process. The continuous variables will be showed as the mean ± standard deviation and performed with a paired samples *t*-test or independent *t*-test. The categorical variables will be presented as percentage (%), and performed with Pearson Chi-squared test. For all comparisons, if a *P*-value is less than .05, the difference is considered statistically significant.

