### Inclusion criteria

2.2

(1)Meet the international standard for neurological classification of SCI developed by American Spinal Injury Association: Grades B to D, confirmed by computed tomography (CT) or magnetic resonance imaging (MRI)^[44]^; or meet the diagnostic criteria for cerebral hemorrhage,^[45]^ confirmed by CT or MRI; or meet the diagnostic criteria for cerebral infarction,^[46]^ confirmed by CT or MRI;(2)Meet the Roman IV diagnostic criteria for functional constipation^[47]^;(3)With symptoms of anxiety and depression;(4)Aged 20 to 80 years;(5)With stable vital signs, clear consciousness, normal communication, and expression skills;(6)Sign an informed consent form and submit to the arrangements of the subject group.

Note: Only patients who meet the above 6 criteria can be included in this study.

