### Randomization and blinding

2.4

Randomization will be based on a randomization sequence generated by the software SPSS25.0. Patients will be randomized at a 1:1 ratio into intervention group and control group. Randomization will be performed by a statistician who is not involved in this study. Data managers, and outcome assessors will be unaware of the outcome. However, due to the trail's nature, the doctors, nurses, and therapists will not be blinded.

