##### Intervention group

2.5.1.2

Receiving the therapy of “combination 3 methods progression” in addition to usual rehabilitation care.

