#### Plans for assessment and collection of outcomes

2.6.1

Demographic and baseline data will be measured by questionnaires before the interventions. The primary outcome and secondary outcomes will be measured by checklists or scales. They will be assessed before the interventions, after 2 weeks of interventions and after 4 weeks of interventions.

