#### Primary outcome

2.6.2

The primary outcome is the number of spontaneous bowel movement per week. It is defined as the number of spontaneous and complete bowel movement without the need of medication or manipulation. The trial investigator will use diary cards to count the number of spontaneous bowel movement in a week.

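### Section 2.9 names only paired or independent t-tests: the between-arm test makes no adjustment for the measured baseline, and the within-arm test is not marked as descriptive

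*Protocol article*

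**What the plan says.** Section 2.9 (Statistical analysis) states: "The continuous variables will be showed as the mean ± standard deviation and performed with a paired samples" t-test or an independent t-test. It does not say which test belongs to which comparison, or whether the independent test uses week-4 values or changes from baseline. One rule then covers everything: "For all comparisons, if a *P*-value is less than .05, the difference is considered statistically significant".

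Section 2.6.2 defines the main endpoint: "The primary outcome is the number of spontaneous bowel movement per week". On timing, section 2.6.1 says of the primary and secondary outcomes: "They will be assessed before the interventions, after 2 weeks of interventions and after 4 weeks of interventions". A baseline value of each outcome will therefore be available.

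The design is parallel (section 1.3), and section 2.4 says "Patients will be randomized at a 1:1 ratio into intervention group and control group". Both arms get four weeks of usual rehabilitation care, because the intervention arm is described as "Receiving the therapy of “combination 3 methods progression” in addition to usual rehabilitation care" (section 2.5.1.2). Entry under section 2.2 requires current functional constipation and also "With symptoms of anxiety and depression".

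**The concern.** Two things are at stake.

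**Precision.** With 60 patients, the baseline value of the same outcome is usually the most useful covariate available, and here it costs nothing to collect. Neither named test adjusts for it as a covariate. The comparison then carries variance that could be removed, and a chance baseline difference between small arms stays in a week-4 estimate.

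**What the paired test answers.** In a 1:1 parallel trial with no matching described, a paired test can only compare before with after inside one arm. It does not compare treatments. Patients enter while symptomatic and both arms receive active care, so some improvement in both arms is plausible even if the added therapy does nothing. Section 2.9 joins the two tests with a plain alternative, puts them under one significance rule, and does not say that the between-arm test decides.

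**Working it through.** **Inputs from the article.** 30 patients per arm (section 2.8); two-sided 5% level (section 2.8 uses 1.96); outcomes at baseline, week 2 and week 4 (section 2.6.1).

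**The plan's own figure.** The section 2.8 formula with P = (0.85 + 0.50)/2 = 0.675 and a difference of 0.35 gives 2 × (1.96 + 0.84)² × 0.675 × 0.325 / 0.35² = 28.08, so the stated 28 per arm reproduces. It rests on a binary effective rate. It supplies no standard deviation, no standardised effect and no correlation for the weekly count.

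**Assumptions, since the article gives no values.** r = 0.3, 0.5 and 0.7; a standardised effect d = 0.6 for the power illustration; a common improvement in both arms of 0.2, 0.5 or 0.8 SD; equal SD before and after; normal data.

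**Step 1: precision.** Relative to a t-test on week-4 values (variance 1), a t-test on change scores has variance 2(1 − r), and ANCOVA has variance 1 − r². The equivalent gain in patients from ANCOVA is 1/(1 − r²) against week-4 values, and 2(1 − r)/(1 − r²) = 2/(1 + r) against change scores.

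| r | ANCOVA variance | gain vs week-4 t-test | gain vs change-score t-test |
|---|---|---|---|
| 0.3 | 0.91 | 1.10 (10%) | 1.54 (54%) |
| 0.5 | 0.75 | 1.33 (33%) | 1.33 (33%) |
| 0.7 | 0.51 | 1.96 (96%) | 1.18 (18%) |

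**Step 2: power at 30 per arm, d = 0.6.** For the week-4 t-test, the noncentrality is 0.6 × √(30/2) = 2.32 on 58 degrees of freedom, and power is 63%. For ANCOVA, the noncentrality is divided by √(1 − r²) and the degrees of freedom are 57. Power is 67% (r = 0.3), 75% (r = 0.5) and 89% (r = 0.7).

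**Step 3: paired test when the therapy adds nothing.** Let both arms improve by m SD. The SD of the change is √(2(1 − r)), so the paired t has noncentrality m × √30 / √(2(1 − r)) on 29 degrees of freedom. For m = 0.5 and r = 0.5 this is 0.5 × 5.48 / 1 = 2.74. The chance of significant improvement in the intervention arm is:

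| common improvement | r = 0.3 | r = 0.5 | r = 0.7 |
|---|---|---|---|
| 0.2 SD | 14% | 18% | 28% |
| 0.5 SD | 61% | 75% | 93% |
| 0.8 SD | 95% | 99% | 100% |

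A simulation of 40,000 trials at r = 0.5 and m = 0.5 gave 76% for the paired test and 4.98% for the between-arm t-test. In 19% of those trials the intervention arm was significant and the control arm was not, a pattern often misread as benefit.

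**The case against.** The best reply is that nothing in section 2.9 is invalid, and most of it stands.

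- **Validity.** A reader might infer that the unadjusted t-test biases the result. It does not: in a randomised 1:1 comparison it holds its 5% error rate. The loss is efficiency only, and it shrinks to almost nothing against a week-4 t-test if r is near zero.
- **Use of baseline.** A reader might also infer that baseline is ignored altogether. The article does not say so, since the independent test may be meant for change scores. Both readings are therefore shown above. ANCOVA is more precise under either, by an amount that depends on r.
- **Within-arm results as efficacy.** It is tempting to say that the plan will report a within-arm P below .05 as proof of benefit. The rule only calls such a difference statistically significant. The trial is described as controlled and its sample size is a two-arm comparison, so the paired tests may be intended as description. What stands is that the text does not say this.
- **Improvement in both arms.** For the primary outcome this is plausible but unquantified. Section 2.6.2 counts only movements without medication or manipulation, so movements produced by laxatives, suppositories or enemas in usual care do not count. The anxiety and depression entry criterion bears on secondary outcomes. Hence the range starts at 0.2 SD.
- **Missing data and analysis sets.** The article's silence on patients without a week-4 value is not held against it. A condensed article commonly leaves this to the full protocol or analysis plan, which is not shown.

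**Conclusion.** The point holds as a matter of efficiency and of an undesignated deciding test, not of bias. Section 2.9 does name its tests, so this is a choice the article makes and not a detail it defers.

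For r between 0.3 and 0.7, the precision forgone is worth 10% to 96% more patients if the t-test is on week-4 values, and 54% down to 18% if it is on changes. At d = 0.6 and 30 per arm, power would rise from 63% on week-4 values to between 67% and 89%. The false signal from the paired test is conditional on its being read as efficacy. It then ranges from 14% to almost 100% over the assumed shifts and correlations, against 5% for the between-arm test. The values of r, d and the common shift are all assumptions, so the ranges matter more than any single figure.

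**What to change.** Reword section 2.9 before any data are analysed:

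- State that the single deciding analysis is the between-arm difference in the week-4 weekly number of spontaneous bowel movements, estimated by ANCOVA with the baseline count as covariate and reported with a 95% confidence interval.
- Use the same model for the anxiety, depression and self-efficacy scores, each with its own baseline value.
- State that paired before/after tests are descriptive only and are not evidence of efficacy.

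The baseline values are already scheduled, so no new data are needed. The cost is a few sentences and one degree of freedom (57 instead of 58 with 30 per arm).

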### Plans to give access to the full protocol, participant-level data, and statistical code

2.10

The time of sharing data and the full protocol is within 6 months after completion of the trial. The full protocol will be published in a peer-reviewed journal.

### Dissemination plans

2.11

We will submit the results of the study to be published in a peer-reviewed journal.

## Discussion

3

As far as we know, this is the first study to evaluated the effect of “combination 3 methods progression” in treating constipation in NBD patients. As an important part of NBD patients, the health problems of SCI patients and stroke patients have been paid more and more attention. SCI was not only considered to be an incurable condition, but also an inestimable public health issue.^[55–58]^ Several studies have shown that SCI was a disease with a high rate of disability and death.^[59,60]^ In China, the incidence of SCI was approximately 23.7 to 60.0 cases per million population, with a relatively rapid growth trend.^[61]^ In addition, stroke has similar disease characteristics. Fifteen million people worldwide suffer a stroke each year, resulting in 5 million deaths and 5 million permanent disabilities.^[62]^ In low-to-middle-income countries, the incidence of stroke continues to increase, accounting for 85% of the world's stroke burden.^[63]^ Patients with NBD will experience a long recovery period, which places a huge financial burden on their family and society. Therefore, it is vital to identify safe and effective treatment methods to solve constipation problem.

TCM and Western medicine have their own unique advantages in the treatment of chronic diseases. Clinical studies have shown that a single treatment modality for constipation symptom in NBD patients cannot achieve satisfactory results.^[64]^ The therapy of “combination 3 methods progression” combines pestle needle therapy with Tuina and functional exercise to form a unique and comprehensive rehabilitation program. The advantages of the therapy are clear: ①The pestle needle overcomes the disadvantage of traditional acupuncture piercing the skin, avoids patients’ fear and the risk of infection, and greatly improves patients’ compliance. ②Low cost of treatment, reducing financial pressure on patients. ③ The operations are very easy and flexible to perform. ④It has no side effects and is highly safe. Because of this, we have also made some achievements in the previous clinical studies.

In conclusion, we believe that this randomized trial will provide more evidence regarding whether the therapy can reduce constipation, anxiety, and depression in NBD patients.
